**Additional site-specific information related to potential interventions – Malawi:**

The ideal schedule for a series of intervention sessions ranged from once a week to once a month, and the time most commonly preferred for the intervention sessions to begin ranged from the day of diagnosis through one week post-diagnosis. Participants with AHI indicated that abstinence after diagnosis might be possible with appropriate counseling. However, participants acknowledged that both desire for sex and non-disclosure to partners will be barriers. Participants with AHI also indicated that a 100-percent rate of condom use post-diagnosis might be possible. Barriers they identified included the need to disclose and the difficulty in using condoms in steady relationships in which condoms had not been used previously. The following potential topics for intervention were also commonly mentioned:

- Abstaining from sex
- How to be safer during sex
- Worries about getting a sexually transmitted infection
- Future relationships
- Feeling afraid of one's partner

**Additional site-specific information related to potential interventions – South Africa:**

Participants mentioned the importance of having a place to talk about their diagnosis and having supportive people who can listen to them, particularly in a climate where stigma surrounding HIV can make many people feel isolated and alone. Most participants reported that they do not think it is possible to abstain from sex for three months after diagnosis with AHI. The majority of participants did think it would be possible to use condoms consistently for a three-month period during AHI. However, a number of barriers to condom use were reported – for example, lack of motivation to use condoms, male partners refusing to use condoms, lack of knowledge about how to use condoms correctly, lack of trust in condoms, and the desire to have children. The following potential topics for intervention were also commonly mentioned:

- Talking with ones partner about sex
- Nutrition and healthy living
- Having a baby when HIV positive

**Issues related to disclosure of HIV status:** The vast majority of participants with AHI disclosed their status to someone -- a sexual partner, family member, or friend -- in the period after diagnosis. Participants were concerned about rejection, gossip, and rumors as a consequence of disclosure. They said that interventions could help people with AHI determine the best way to disclose their status to their families and partners.

**Issues related to partner notification:** Extensive data were collected on the advantages, disadvantages, preferences, and perceived partner reactions to partner notification approaches from individuals with acute HIV infection, partners of individuals with established HIV infection, research staff, community leaders, and individuals with established HIV infection. Finding included that participants said that people should be informed of their partners' HIV status. Advantages and disadvantages of both approaches were identified. In Malawi, although support for patient notification did not strongly outweigh support for provider notification among the participant groups, more individuals with AHI in Malawi preferred patient notification. In South Africa, individuals with AHI preferred patient and provider notification equally. In both sites, participants suggested couples counseling as another approach to partner notification where partners be tested together, even if one partner has already learned his/her status. Participants in both sites also commonly expressed the fear that partners could respond negatively and that they could experience stigma as a result of partner notification. In Malawi, while violent reactions to disclosure were not reported during the interviews with participants with AHI, disclosure often led to the termination of relationships. Among this group of participants with AHI, several female partners chose to leave their male partner after he was diagnosed with acute HIV

infection. Overall, fears of partner's reactions and fears of discrimination from family/friends/community hindered disclosure (as did the perceived limited opportunities to disclose one's status). In South Africa, participants with AHI were also concerned about rejection, gossip and rumors as a consequence of disclosure. A single participant experienced a social harm event related to her partner disclosing her status to others.

Given diverse perspectives and individual situations, a combination of approaches to partner notification may be needed; offering the option of provider-assisted notification may be helpful.

In summary, the CHAVI 011 data suggest that participants with AHI would accept a counseling intervention focused specifically on changing behavior during the acute phase of HIV infection to avoid transmission of HIV to uninfected partners. As presented above, participants identified several topics that should be included in such a counseling intervention and these are integrated into the intervention developed for HPTN 062.

### **1.3 Study Rationale**

Individuals with acute or early HIV infection may be responsible for a substantial proportion of onward transmission of HIV infection, especially in sub-Saharan Africa. Several recent modeling studies have addressed this issue with varying results (Hollingsworth, Anderson, et al., 2008; Pinkerton 2008; Abu-Raddad, Longini; 2008). However, such individuals are widely believed to be more than 20 times more infectious than those with established/chronic HIV. Researchers generally believe that transmission from individuals with AHI accounts for a substantial share of new cases, depending on a number of factors such as stage of the epidemic and partnership patterns.

Existing technology makes it difficult to identify large numbers of individuals with AHI. However, future technological advances in HIV testing will make it easier to identify such individuals earlier and in larger numbers. Currently, rapid HIV tests are being developed to identify individuals very soon after infection. As these new technologies become available, data on behavioral interventions designed specifically for individuals in the acute phase of infection will be needed. HPTN 062 will pilot and evaluate an intervention designed specifically for this purpose. Given the substantial infrastructure required to identify individuals with AHI, HPTN 062 will be implemented ancillary to and in parallel with CHAVI 001, an acute HIV-1 infection prospective cohort study in sub-Saharan Africa.

The HPTN 062 intervention is different from the standard-of-care counseling being provided as part of CHAVI 001. While many of the topics provided in the HPTN 062 intervention are the same as those covered in CHAVI 001, the approach used to discuss these topics is quite different (e.g., motivational interviewing). HPTN 062 also includes a wider array of topics than is covered in standard CHAVI 001 counseling. Role playing, skills building, and other activities will be implemented to foster self-efficacy and to increase motivation to practice safer sex. These approaches/techniques are not part of standard counseling offered through CHAVI 001. Based on the information available from CHAVI 001, no counseling scripts exist with specific messages for AHI. Therefore, the enhanced HPTN 062 intervention is different from the standard counseling offered through CHAVI 001 in the following ways: It is systematic, theory-based, aims to enhance skill-building, provides more in-depth information, includes development of a patient-focused risk-reduction plan, and allows more time for the key topics to be covered.

The proposed intervention is different from existing "positive prevention" programs in that no current interventions focus specifically on the acute or early phase of HIV infection. While components of the HPTN 062 intervention are similar to other skill-building approaches being

used in positive-prevention programs, the HPTN 062 intervention incorporates empirical data on sexual behavior among individuals with AHI, including desires for interventions and understanding of AHI. Thus HPTN 062 focuses on issues identified as most salient to these individuals. In addition, the timeframe in which the intervention is being delivered is a key feature distinguishing it from existing positive-prevention programs. Specifically, the HPTN 062 intervention starts on the day that participants are informed of their AHI diagnosis, at a time when they are highly infectious and thus concentrating primarily on reducing risk during a targeted versus indefinite period. For individuals diagnosed with acute or early HIV infection through studies or screening programs, there is an ethical imperative to provide guidance for behavior change to limit transmission to uninfected partners, particularly during this highly infectious phase.

## **2.0 STUDY OBJECTIVES AND DESIGN**

### **2.1 Primary Objectives**

1. To evaluate the feasibility of enrolling and delivering an enhanced individual-level counseling intervention to individuals in the acute and early phases of HIV infection.
2. To evaluate the acceptability of an enhanced, individual-level counseling intervention among individuals in the acute and early phases of HIV infection

### **2.2 Secondary Objectives**

1. To examine the effectiveness in reducing risk behaviors for HIV transmission of an enhanced, individual-level counseling intervention aimed at individuals in the acute and early phases of HIV infection.
2. To examine participant risk behaviors for HIV transmission and participant perceptions of infectiousness after the acute and early phases of HIV infection

### **2.3 Study Design**

This is a multi-site, two-arm, randomized, prospective study to evaluate the feasibility and acceptability of a counselor-delivered behavioral intervention for individuals identified as having AHI or early HIV infection.

Individuals in the acute/early phase of HIV infection who are participating in CHAVI 001 will be recruited for HPTN 062. For the purposes of this study, the following definition of AHI from CHAVI 001 will be used:

Documentation of the following within 45 days of enrollment:

- Concordant negative or discordant HIV antibody tests using two different rapid HIV tests, OR a negative HIV EIA test
- AND
- Positive nucleic acid test (NAT)

After being informed of their diagnosis of AHI, participants in both study arms will receive the same standard post-test HIV counseling aimed at risk reduction in conjunction with HIV testing through CHAVI 001. Individuals enrolled in CHAVI 001 who are interested in participating in

HPTN 062 will go through the process of informed consent for HPTN 062. Participants will then be randomized in a 1:1 ratio to one of two study arms. All participants will be followed for 6 months post-enrollment. Participants in both arms will receive standard HIV risk-reduction counseling at weeks 1-4, 8, 12, 16, 20 and 24 through CHAVI 001. (This is in accordance with standard CHAVI 001 procedures.) See section 4.2 for a description of standard risk-reduction counseling

Participants randomized to the experimental arm will take part in four enhanced individual counseling sessions (from enrollment to week 2) which aim to help reduce the risk of sexual transmission of HIV to their uninfected partners, particularly during this highly infectious initial stage. The introductory session will be delivered after the participant has been informed of his/her diagnosis, has received post-test counseling through CHAVI 001, and has provided informed consent for HPTN 062. Three subsequent sessions (sessions 2, 3 and 4) will be delivered between the introductory session and week 2. The fifth session -- a booster and the final session of the series -- will be provided at week 8. This session will focus on maintenance of risk-reduction behaviors during the established phase of HIV infection. See Section 4.1 for a description of the experimental intervention sessions. During the last 4 months, participants in both arms will be followed monthly to collect information on behavior change and perceptions post-intervention. HIV risk behaviors and perceptions will be compared across the two arms of the study. The feasibility and acceptability of the experimental intervention will be evaluated.

Note: While the burden on individuals who have recently been diagnosed with HIV must be limited, this concern must be balanced with the need to provide prevention messages for individuals with AHI as soon after diagnosis as possible to maximize the benefit in reducing HIV transmission. Formative data from CHAVI 011 suggests that individuals want to talk with someone about their diagnosis; individuals reported wanting an intervention during the acute phase of infection.

Note: Acknowledging the small sample size of the study, inclusion of a randomized comparison offers a number of advantages over a non-randomized, non-controlled study design. Without a comparison group, there could be no assessment of whether any differences in behavior observed over time may have resulted from the intervention. Another advantage is that it will allow for assessment of an effect size, which will be valuable if a larger study is to be conducted. Non-randomized, non-controlled trials are also more susceptible to bias and confounding.

All participants will be asked a behavioral assessment at enrollment (baseline) and at weeks 1, 2, 4, 8, 12, 16, 20 and 24. The behavioral assessment will be conducted prior to the CHAVI counseling sessions, except at baseline, when the assessment will be conducted after the CHAVI post-test counseling. Topics that may be covered are listed in Table 4. A brief post-session quantitative assessment will be administered to participants after each experimental intervention session (for the experimental group) and after each standard-of-care counseling session at enrollment and at weeks 1 and 2 (for the control group) to collect information about the acceptability of each individual session (i.e., content, format, and perceived effectiveness) and to document topics discussed. A separate post-session questionnaire will also be administered to each arm at different assessment time points and will cover HIV knowledge, risk perceptions and self-efficacy.

An in-depth interview (e.g. qualitative semi-structured interview) will be conducted with participants at weeks 2, 8, 12, and 24, in both arms. At the week 2 interview, questions will primarily focus on participants' perceptions on the format, content, and effectiveness of either the experimental intervention sessions or the standard-of care counseling sessions, depending on their

assigned study arm, in order collect more descriptive information on the acceptability of the intervention. For participants in the experimental arm, they will also be asked to describe whether or not they perceive any further benefit from attending the experimental intervention sessions in addition to the standard-of-care counseling they received. Questions on sexual behavior will be asked as appropriate to enhance the quantitative data collected on intervention effectiveness and on sexual behavior and perception. At the week 8, 12, and 24 interviews, questions will primarily focus on gathering more in-depth information on sexual behavior and on perceptions of risk behavior with an emphasis on investigating changes in participants' risk-reduction behavior as they transition from the acute/early phase of infection into established infection. All qualitative interviews will be audio taped if permission is granted by the participant.

The behavioral assessment will be administered prior to counseling (except at baseline) by staff other than the counselor, in order to reduce a patient's inclination to provide socially desirable responses to questions about his/her sexual behavior.

Note: Information on social harms will be collected as part of CHAVI 001. In addition, social harms judged to be significant by the Investigator of Record will be reported to the relevant IRB/ECs at least annually, or according to their individual requirements.

**Counselor Interviews:** It is anticipated that one counselor will deliver the experimental intervention at each site; however, sites may choose to have more than one counselor deliver the intervention. Written informed consent will be obtained from the counselor(s) who deliver the experimental intervention (see Appendix II B for a sample study consent document for counselors) prior to participation in the interview. Approximately three qualitative interviews will be conducted with each counselor(s) at each site to capture their perceptions of the acceptability and perceived impact of the intervention over the course of the study. Topics that will be explored include: perceived effectiveness of the intervention, strengths and weaknesses of the intervention, areas for improvement, challenges of delivering the intervention, challenges of following the experimental intervention curriculum, perceptions of participants' experiences, and other topics related either to the content, format, perceived effectiveness of the intervention, or perception of the participants' experiences.

Both the counselors who deliver the experimental intervention and the counselors/clinicians who provide standard counseling as part of CHAVI 001 will complete a brief quantitative assessment at the end of each session to document topics covered in each session and the goals set. This assessment will take place after every intervention session in the experimental arm, and at baseline, week 1 and 2 in the control arm. Counselors will also provide a summary of the session discussions, including strategies discussed.

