##### **Format**

###### **Primary**

- Acceptability of when to start the intervention (at the time the participant is informed of the diagnosis or later)
- Acceptability of session length
- Acceptability of number of sessions
- Acceptability of session spacing

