**Content**

- Perceived satisfaction of each session

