**Perceived effectiveness of session**

- Perceived helpfulness of each session

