## 7.6 Analysis Plan

### 7.6.1 Primary Analysis

#### 7.6.1.1 Analysis of Feasibility

Feasibility will be evaluated by the following:

- 1.) The proportion of enrolled participants in the experimental arm who attend the first 4 intervention sessions in the first 2 weeks after enrollment out of all individuals randomized to the experimental arm. An estimate of the proportion is given by

$$P = \frac{A}{N}$$

where N is the total number of participants enrolled in the experimental arm and A is the number of individuals who attend the first 4 intervention sessions in the first 2 weeks among those N participants. Since the sample size is not large (about 23 per arm), the exact binomial confidence interval will be calculated for the estimated proportion.

2.) The proportion of enrolled participants in the experimental arm who attend the 4 intervention sessions and the fifth, booster session out of all individuals randomized to the experimental arm, and compared to the proportion of individuals who attend their CHAVI 001 visits at weeks 1, 2, and 8. The two-sided Fisher exact test will be used to test 2 proportions.

3.) The proportion of enrolled participants in the experimental arm who attend the first 4 intervention sessions at any time point after enrollment out of all individuals randomized to the experimental arm. This analysis will include participants who attended all of the first four intervention sessions but not necessarily within the 2 week period after enrollment. An estimate of the proportion is given by

$$P = \frac{A}{N}$$

where N is the total number of participants enrolled in the experimental arm and A is the number of individuals who attend the first 4 intervention sessions at any time point among those N participants.

Feasibility endpoints will be measured using session attendance records. Data from the quantitative assessments and qualitative interviews will not contribute to the analysis of the feasibility endpoints.

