#### 7.6.1.2 Analysis of Acceptability

Data from the quantitative assessment and qualitative interviews will contribute to the analysis of the acceptability endpoints. Standard descriptive statistics, such as means, medians, variance, and interquartile ranges for continuous variables and proportions for binary variables will be used to summarize the format, content, and perceived effectiveness. For categorical variables, the numbers and the proportions will be tabulated. Analysis of the qualitative data related to acceptability is described below in Section 7.6.3 Qualitative Analysis.

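### Quantitative acceptability ratings come only from attended sessions, so later-session and whole-course format ratings may overstate acceptability among those offered the intervention

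*Protocol*

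**What the plan says.** Section 2.3 sets the timing of the quantitative acceptability form: "A brief post-session quantitative assessment will be administered to participants after each experimental intervention session". In the control arm it follows the standard counseling sessions at enrollment and weeks 1 and 2. Appendix I shows it only in the participant post-session row.

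Section 7.2.1 lists four primary format measures: when to start, session length, number of sessions ("Acceptability of number of sessions") and spacing. Content and perceived effectiveness are defined session by session: "Perceived satisfaction of each session" and "Perceived helpfulness of each session".

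There is a second source, also in section 2.3: "An in-depth interview (e.g. qualitative semi-structured interview) will be conducted with participants at weeks 2, 8, 12, and 24, in both arms". The week 2 interview deals mainly with the format, content and effectiveness of the sessions. The later interviews deal mainly with sexual behavior and risk perception.

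Section 7.6.1.2 uses both sources. Standard descriptive statistics "will be used to summarize the format, content, and perceived effectiveness", and no denominator is named. The feasibility proportions in section 7.6.1.1 do have one, "where N is the total number of participants enrolled in the experimental arm".

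**The concern.** A person who finds the sessions too many, too long or too close together can simply stop coming. From then on that person completes no further post-session form. This matters most for number and spacing, which can be judged properly only over the whole course, and on which people who stop early are especially informative.

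At stake is one of the two primary objectives. A favorable rating of the format could partly reflect who was still there to give it, and so mislead the design of a larger study. An analysis plan could set the denominator later, but it cannot recover ratings that were never collected. The collection schedule is fixed in this protocol.

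**Working it through.** **1. Where acceptability could be rated quantitatively.**
- Post-session form (Appendix I): enrollment, day 3 (experimental arm), weeks 1 and 2, and week 8 (experimental arm). In the experimental arm, section 2.3 ties each completion to an intervention session.
- Separate post-session questionnaire (section 2.3): HIV knowledge, risk perceptions and self-efficacy, not acceptability.
- Visit-based behavioral assessment (section 2.3, with topics in Table 4): outcomes, mediators and moderators. No acceptability item is listed, although Table 4 gives examples and is not exhaustive.

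As written, then, the quantitative ratings depend on attendance.

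**2. The plan's own precision figure.** The protocol gives no figure for acceptability. Its exact binomial example in section 7.3 is an observed proportion of 0.8 with n = 23, 95% CI (0.58, 0.94). The Clopper-Pearson interval with x = 0.8 × 23 = 18.4 is (0.582, 0.936), which agrees. All 25 cells of Table 5 reproduce to within 0.005.

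**3. Size of the selection effect.** Let a be the share attending, qA approval among attenders and qN approval among non-attenders.
- Approval among all randomized = a·qA + (1 − a)·qN
- Attender-only figure minus this = (1 − a)·(qA − qN)

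The attender-only figure is too high only if qN is below qA.

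**4. Illustration.** N = 23 is from section 7.3. Attendance of 18 and approval by 17 of those 18 are assumed. The 0.8 in section 7.3 refers to completing four sessions in two weeks, not to attending one session. It shows only that 18 of 23 is of a plausible order.

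| Quantity | Estimate | Exact 95% CI |
|---|---|---|
| Attenders only | 17/18 = 94% | 73% to 100% |
| All randomized, no non-attender approves | 17/23 = 74% | 52% to 90% |
| All randomized, every non-attender approves | (17 + 5)/23 = 22/23 = 96% | 78% to 100% |

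Check by the formula:
- qN = 0: (5/23)(17/18 − 0) = 0.205, about 20 points too high
- qN = 1: (5/23)(17/18 − 1) = −0.012, about 1 point too low

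The range among all randomized is 5/23 = 22 points wide, or 1/23 = 4.3 points per missing rater.

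**5. Range over other assumptions, with qA = 0.9.**

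| a | qN = 0 | qN = 0.3 | qN = 0.6 | qN = 0.9 | qN = 1.0 |
|---|---|---|---|---|---|
| 0.9 | +0.09 | +0.06 | +0.03 | 0 | −0.01 |
| 0.8 | +0.18 | +0.12 | +0.06 | 0 | −0.02 |
| 0.6 | +0.36 | +0.24 | +0.12 | 0 | −0.04 |

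The possible error is much larger upward than downward, but its actual value depends on qN, on which the protocol has no information.

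**The case against.** The strongest reply is that the protocol does ask many of these people.
- The form is completed after every session and covers format. Someone who stops after session 1, 2 or 3 has already rated one to three times, and only a person who attends no session gives no rating.
- The week 2 interview is tied to the visit, covers both arms, asks about format and feeds the acceptability endpoints. Section 7.6.3 limits changes to the acceptability questions so that answers stay comparable.
- Non-attendance is reported openly as primary feasibility, out of all randomized to the experimental arm.
- Missed sessions can be made up (section 5.2), and section 3.5 calls for an attempted final assessment of early leavers and recorded reasons for withdrawal.
- Satisfaction with, or helpfulness of, a session that never took place is undefined. Scoring non-attenders as not accepting it would largely repeat the feasibility endpoint.

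Most of this stands, and it narrows the point. It does not remove it. A rating after session 1 says little about the number and spacing of a course not yet experienced. Interview material is coded into themes (section 7.6.3) and gives no proportion to set beside the ratings. Week 2 is also the target visit for session 4, so a person who misses that visit may miss both. The final assessment has no stated content, and it covers people who leave the study, not those who stay and skip sessions. Attendance records do not say why a session was missed.

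A reader might also infer that section 7.6.1.2 prescribes an attenders-only denominator. It names none, and that choice may be made in an analysis plan not shown here.

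**Conclusion.** The point holds for the quantitative ratings of later sessions and of the whole-course format items. These come from whoever was still attending and are likely to overstate acceptability among those offered the intervention. In the illustration, 94% among attenders is compatible with 74% to 96% among all randomized. That rests on assumed attendance and approval, and the 74% end assumes that no non-attender would approve.

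Two stronger readings are tempting, and the documents support neither. One is that acceptability is measured only among attenders: the interviews also contribute, and early drop-outs have usually rated some sessions. The other is that the result is biased upward as a matter of fact: the direction depends on why sessions are missed, and the error is zero if non-attenders think as attenders do. This is a worthwhile correction to the data collection for a primary endpoint, and it does not invalidate the acceptability assessment.

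**What to change.** **Collection (section 2.3 and Appendix I).** Ask every experimental-arm participant, however many sessions attended, the four primary format items (start time, length, number, spacing) and the reason for any missed session. Use a scheduled form that does not depend on intervention attendance. The week 4 participant assessment suits this, because it falls after the planned first four sessions and is not itself an intervention visit. Put the same items on the final assessment of early leavers in section 3.5.

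**Analysis (section 7.6.1.2).** Show each rating with the number of raters out of all randomized to the experimental arm. For the four format items, add an exact confidence interval and, as a sensitivity analysis, a range in which non-raters are counted first as all accepting and then as none accepting. Keep satisfaction and helpfulness of each session among those who attended it.

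**Cost.** A few more items on an existing form, a few lines of analysis text and no new visit. The reported figure may be less favorable, and the worst-case end is deliberately conservative. People who stop all contact will still be missed, but the raters-out-of-randomized count will show how many they are.
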